### Study sample size for a mixture of individually and cluster-randomized designs

For those designs involving cluster randomization, the number of events needed to assess efficacy and sample sizes would be increased to account for the correlation within clusters. While the intraclass correlation coefficient (ICC) parameter for continuous and binary outcomes is commonly used, it is not easily extended to time-to-event outcome settings because of the presence of censoring (e.g. losses-to-follow-up, end-of-study administrative censoring).^
15
^ It has been shown that ICC estimators based on censoring indicators or observed event times can be negatively biased.^16,17^

One way to account for the clustering effect is using an ICC based on the binary event indicator and to inflate the events required by the usual design effect that equals 1 + (*m −* 1) ICC, where *m* is the average cluster size.^
18
^ For the Ebola ring vaccination trial in Guinea, the average ring size was about 80, and the ICC was about 0.05, resulting in a design effect of about 4. Thus, 600 total events would be needed for the design above, resulting in 150 effective events. For mixtures of individually and cluster-randomized designs, the target number of events will be the total number of effective events.

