## Methods

### Operating characteristics of the trial design

A core protocol approach will be used, allowing multiple vaccine candidates to be tested against a shared placebo/control group. The primary objective of the trial will be to evaluate the effect of each vaccine on the rate of virologically confirmed MARV disease, regardless of severity. In some cases, it may also be possible to evaluated MARV infection as a co-primary outcome. Although the study may lack power for formal statistical inference about VE against severe disease or death due to MARV disease, these secondary endpoints will be evaluated and reported for each vaccine. Additional exploratory endpoints will include VE between the first and second dose, for two-dose vaccines. Infecting viruses will be sequenced as much as possible to assess the influence of virus clades and evolution on transmissibility, virulence and VE. A subset of trial participants will provide periodic blood samples. Immune markers measured from participants in this immunogenicity subset will be used to assess immune correlates of risk and protection, and help with the assessment of VE against infection.

The trial is endpoint-driven, as the main analysis for each vaccine arm versus the concurrent shared placebo/control arm is triggered by the occurrence of a total of 150 cases of MARV disease across these two arms. While results from the main analysis will be reported, blinded follow-up will continue to evaluate safety and duration of immunity. This fixed number of 150 endpoints provides 90% power to rule out the hypothesis that VE is ≤ 30%, when the true VE is ≥ 60%, where statistical significance would be achieved if the estimated VE were ≥ 50%. In the setting of COVID-19 vaccines, such results would meet or exceed the World Health Organization-Food and Drug Administration (FDA) established threshold for worthwhile VE.

A global data monitoring committee will regularly review the accumulating safety results and major endpoint results. Different candidate vaccines may be available or suitable to enter the trial at different calendar times. Using a shared placebo/control group and a common core protocol to evaluate multiple candidate vaccines in the trial, resources allocated to the evaluation of each candidate vaccine will be judiciously saved while a high standard of scientific rigour and efficiency is ensured.^
10

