## Results

### VE analysis

The primary efficacy endpoint will be analysed as a time-to-event outcome, including only those events that occur 10 days after the final vaccination dose. Such a gap of 10 days is chosen to allow time for the vaccination series to take effect and to reduce the chance of including events occurred prior to the vaccination due of the incubation period for Marburg. All participant-level failure (diagnosis with disease) and censoring events are reported relative to the time of randomization. The time of virologically confirmed (i.e. laboratory-confirmed) MARV disease is the earliest time of reported qualifying MARV disease symptoms that occur within 10 days of virological confirmation of MARV infection. Participants’ follow-up times will be right censored at the time of last contact at which endpoint status was assessed. Cox proportional hazards regression will be used for analysis. VE, measured by one minus the hazard ratio (vaccine versus placebo/comparator), will be the effect measure. Inference will be based on a one-sided logrank test of H_0_
^benefit^: VE ≤ 0.30, using an O'Brien-Fleming boundary for early termination that preserves an experimental (one-sided) 0.025 error rate; the alpha levels would be one-sided 0.0003 at 50 events and one-sided 0.0069 at 100 endpoints, where the remainder of the (one-sided) 0.025 error rate would be spent at the final analysis. Using these O'Brien-Fleming criteria after 50 and 100 events, benefit is established when estimated VE is ≥80% and ≥59%, and lack of benefit, that is, ruling out the target VE of 60% for which the trial has 90% power, is established when estimated VE is ≤−6% and ≤34%, respectively. When estimating VE against infection, the outcome would be infection as measured by time to seroconversion, using interval censoring methods for the estimand. In this case, the operating characteristics of the statistics would be the same as described above.

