### Study sample size for individually randomized designs

The trial is endpoint-driven, as the primary analysis for each vaccine arm versus the concurrent shared placebo/control arm is triggered by occurrence of a total of 150 cases of MARV disease across these two arms. The primary analysis results will be reported but blinded follow-up will still continue. We assume a 1% cumulative attack rate in the control arm over 6 months of outbreak time. The trial period could involve several years of follow-up and across outbreaks. As stated above, there will be two interim analyses at the points when 1/3 and 2/3 of events have occurred, respectively. We use the O'Brien-Fleming-type spending function for both false-positive and false-negative errors. All the sample size calculations were conducted using the R package *rpact*.

For example, with a target level VE of 60%, with 150 total endpoints in a pairwise comparison, there is approximately 90% power to reject VE less than or equal to 30% if true VE is 60%, based on a logrank test with one-sided type I error rate of 0.025. With equal allocation to the active vaccine arm and the control arm, a minimum follow-up of 3 months for the last accrued participant and an annual drop rate of 10%, we calculated sample sizes for different accrual rates (Table 1). If on average 30,000 participants will be accrued each month, we need 18,062 participants per arm and an expected study duration of 9.1 months. Lower accrual rates are associated with longer study durations but smaller sample sizes. Using the sample size of 18,062 per arm, we simulated 100 times exponentially distributed event times without early stopping to investigate the coverage of the two-sided confidence interval of the VE estimate. The average total number of events is 179 and the average 95% confidence interval for the VE is (45%, 71%). The lower confidence bound would exclude 30% with a probability of 0.93, and the point VE estimate is greater than 50% with a probability of 0.91. We performed a sensitivity analysis, varying the accrual rate, assuming a 1% cumulative attack rate in the control arm over a 12-month period with an annual dropout rate of 10%, and a minimum follow-up of 6 months after the last accrual (Table 1). The sample size increases with increasing accrual rate to about 18,062 participants per arm. The best sample size is about 20,000 participants per arm, or about 40,000 participants per vaccine/comparator combination.

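### The design effect for cluster events is about 5, not about 4, on the article's own inputs, so 600 cluster events give about 121 effective events and not 150

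*Protocol article*

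**What the plan says.** The trial is event-driven. The main analysis of each vaccine against control is due at 150 events, sized to reject VE ≤ 30% when true VE is 60%, "based on a logrank test with one-sided type I error rate of 0.025", with about 90% power. The VE analysis section places two interim looks by event count: under its O'Brien-Fleming "criteria after 50 and 100 events, benefit is established when estimated VE is" at least 80% and at least 59% respectively.

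For cluster randomization, the section on sample size for a mixture of designs first warns that "ICC estimators based on censoring indicators or observed event times can be negatively biased". It then offers, as one option, "using an ICC based on the binary event indicator and to inflate the events required by the usual design effect", namely 1 + (m − 1)ICC with m the average cluster size. Its example is the Ebola ring trial: m about 80, ICC about 0.05, design effect about 4, hence 600 total events for 150 effective ones. For mixtures, "the target number of events will be the total number of effective events".

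The section on blending across designs analyses the pooled data with a marginal proportional hazards model under working independence and a robust sandwich variance.

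**The concern.** Once effective events are the target, the conversion from raw to effective events decides when a mixed or all-cluster comparison is analysed. The article gives one conversion and one worked result, and that result does not follow from its inputs. If 600 (or division by 4) is carried into a working protocol, the final analysis comes with less information than the stated power needs.

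Two features of the conversion add uncertainty. It uses only the mean ring size, although rings of contacts and contacts of contacts, households and compounds are unlikely to be equal in size. It also takes an ICC from another disease and trial, of a type that the same section says may be underestimated. The interim VE limits are stated for 50 and 100 events, without saying that these are effective events when the data come from clusters.

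**Working it through.** **Inputs from the article.** Null HR 0.70, alternative HR 0.40, one-sided 0.025, 1:1 allocation, 150 events; m about 80, ICC about 0.05; 7651 participants in 90 rings (Conclusion). **Assumed, because not given:** the coefficient of variation (CV) of ring size, and the ICC in a future Marburg trial.

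**1. The 150-event base.** Schoenfeld power is Φ(½ ln(0.70/0.40) √d − 1.96), with ln 1.75 = 0.5596. At d = 150: Φ(0.2798 × 12.25 − 1.96) = Φ(1.47) = 92.9%. Allowing for the unequal event split under null and alternative gives 90.3%; simulating the stated interim looks gives 92.5%. The claim of approximately 90% is supported.

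**2. The design effect.** 1 + (80 − 1) × 0.05 = 4.95. The stated value of about 4 does not reproduce. It appears only if the leading 1 is dropped (79 × 0.05 = 3.95), or if ICC = 3/79 = 0.038 at m = 80, or if m = 61 at ICC 0.05.

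- Rounding does not explain it. The most favourable corner of m 75–85 and ICC 0.045–0.055 is 1 + 74 × 0.045 = 4.33, where 600/4.33 = 139 effective events.
- The ring trial's own counts give m = 7651/90 = 85.0 and a design effect of 1 + 84.0 × 0.05 = 5.20.

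**3. Consequence at the article's inputs.**

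- Effective events from 600: 600/4.95 = 121.2, which is 81% of 150.
- Events needed: 150 × 4.95 = 742.5, so 743. With m = 85: 150 × 5.20 = 780.
- Schoenfeld power at 121.2: Φ(0.2798 × 11.01 − 1.96) = Φ(1.12) = 86.9%, down from 92.9%. With the interim looks it falls from 92.5% to 86.4%; with event-split variances, from 90.3% to 83.8%.

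**4. Unequal rings.** The usual extension is 1 + [(1 + CV²)m − 1]ICC. At m = 80 and ICC 0.05:

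| Assumed CV | Design effect | Events for 150 effective | Effective events (power) at 743 |
|---|---|---|---|
| 0 | 4.95 | 743 | 150 (93%) |
| 0.3 | 5.31 | 797 | 140 (91%) |
| 0.5 | 5.95 | 893 | 125 (88%) |
| 0.7 | 6.91 | 1037 | 107 (83%) |

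The last column starts from the corrected 743 events, so that it shows ring-size variation alone. From 600 events, CVs of 0.3, 0.5 and 0.7 leave 113, 101 and 87 effective events.

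**5. A different ICC (equal rings, m = 80).** At ICC 0.075 the design effect is 6.92 and 600 events give 87 effective; at 0.10 they give 67. At ICC 0.03 the design effect is 3.37 and 600 events give 178; at 0.02 they give 233. The break-even for 600 events is ICC 0.038.

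**6. A mixture.** As an illustration, 75 individually randomized events plus 300 cluster events count as 75 + 300/4 = 150 by the stated conversion. At 4.95 they are 75 + 60.6 = 135.6, with Schoenfeld power 90%. The loss is diluted but does not vanish.

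**7. Calibration of an information target.** At VE 60% and 1:1 allocation, vaccine events are 0.4/1.4 = 2/7 of the total. The information on the log hazard ratio from d independent events is therefore d × (2/7)(5/7): 10.2, 20.4 and 30.6 at 50, 100 and 150 events. The shortcut of d/4 (12.5, 25, 37.5) assumes an equal split; reaching 37.5 at VE 60% would take 37.5 × 49/10 = 184 independent events.

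**The case against.** The strongest reply is that the article does not commit itself to the 600. The design effect is one option, the ring-trial figures are an example, and how effective events will be counted, including any re-estimation of the ICC, can properly sit in a fuller document. The Conclusion says that cluster randomization is less likely to be chosen and that the blended analysis needs further study. This stands as a limit on reach: all events coming from clusters is the extreme case. It does not repair a printed result that contradicts its own formula and inputs.

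Several stronger readings are tempting, and the article does not support them:

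- *That it admits its ICC is biased low.* It says that a class of estimators can be; it does not say that 0.05 is, or by how much.
- *That 0.05 is fixed as the trigger input.* Nothing says so.
- *That the trigger must fire early.* With equal rings of 80, a true ICC below about 0.038 would make 600 events late.
- *That the type I error is compromised.* The robust variance addresses within-cluster dependence in the test.
- *That interim information fractions must be wrong.* If all events come from clusters, a constant error in the design effect cancels, and looks at one third and two thirds of events remain at those fractions of the final information. The error need not cancel in a mixture whose cluster share changes over time.

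**Conclusion.** The arithmetic error is established from the article alone: the design effect is 4.95, 600 cluster events are worth about 121, and about 743 are needed (about 780 at m = 85). The loss in the all-cluster case is about 6 percentage points of power, from about 93% to about 87% by the Schoenfeld formula, and proportionately less in mixtures.

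The omission of ring-size variation is a real weakness of the formula, and at a given ICC it acts in one direction only; its size rests on assumed CVs. The uncertainty in the ICC runs both ways, so a fixed conversion may trigger analysis early or late. The consequence is for power and the timing of looks. This should be corrected before the event target is used in a working protocol.

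**What to change.** - Restate the design effect as about 5 and the all-cluster target as about 743 events, or keep 600 and state the lower power.
- For planning, use 1 + [(1 + CV²)m − 1]ICC over a stated range of CV and ICC, including ICC values below 0.05.
- For cluster data, time the interim and final looks on observed information from the robust variance of the log hazard ratio, or on a pre-specified blinded re-estimate of the ICC and ring-size CV. If the ICC is re-estimated, name the estimator, given the article's own warning about bias.
- Calibrate any information target to the expected event split (about 10.2, 20.4 and 30.6 at VE 60%), not to a quarter of the event count, which would delay even an individually randomized comparison beyond 150 events.
- State in the VE analysis section that the 50- and 100-event looks mean effective events when data come from clusters.

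The cost is protocol wording and, if information timing is chosen, a variance calculation by an unblinded statistician serving the data monitoring committee. The downside is that the raw event total for cluster recruitment becomes larger and is not known in advance.

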**Results::**

The primary efficacy endpoint will be analysed as a time-to-event outcome. A vaccine will be considered successful if its estimated efficacy is greater than 50% and has sufficient precision to rule out that true efficacy is less than 30%. This will require approximately 150 total endpoints, that is, cases of confirmed Marburg virus disease, per vaccine/comparator combination. Interim analyses will be conducted after 50 and after 100 events. Statistical analysis of the trial will be blended across the different types of designs. Under the assumption of a 6-month attack rate of 1% of the participants in the placebo arm for both the individually and cluster-randomized populations, the most likely sample size is about 20,000 participants per arm.

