## Conclusion

We have described a vaccine trial design for identifying an efficacious MARV vaccine as rapidly and efficiently as possible. This event-driven, platform trial design takes into account the potential sporadic spread of MARV over a wide range in Sub-Saharan Africa. The design incorporates elements of the successful ring vaccination trial structure that was employed to find an efficacious vaccine for Ebola in 2015 in Guinea.^23,24^ In that trial, a vesicular stomatitis virus-based vaccine expressing a surface glycoprotein of Zaire Ebolavirus was found to be safe and highly efficacious at the interim analysis with 90 clusters (i.e. rings), 48 with immediate vaccination and 42 with delayed vaccination, comprising a total of 7651 participants. For MARV, there have been 13 outbreaks since 1967.^
25
^ Most of these outbreaks have been small, with fewer than 30 cases. However, the 2005 outbreak in Angola had 374 cases, and the 1998–2000 outbreak in the Democratic Republic of the Congo totalled 154 cases. Both of these outbreaks would have passed the threshold of 150 cases needed to carry out a final analysis with the vaccine trial design described here. The timing and size of future MARV outbreaks remains uncertain, but as mentioned above, there is evidence of increased circulation of MARV in Central and Western Africa. In addition, there are a host of other potential filovirus and other infectious disease threats, with epidemic and pandemic potential, that could emerge without warning.^
9
^ The vaccine trial design described here could be quickly implemented should any of these threats emerge, although it could take several outbreaks to accumulate enough evidence to assess the efficacy of the vaccines deployed in the trials.

Currently, the World Health Organization COVID-19 Solidarity Vaccines trial^
7

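### The stated ring size and ICC give a design effect of 4.95, not about 4, so 600 cluster-randomised events are worth about 121 effective events rather than 150

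*Protocol article*

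**What the plan says.** The protocol article's section on sample size for a mixture of individually and cluster-randomized designs gives the method: "inflate the events required by the usual design effect that equals 1 + (*m −* 1) ICC", with m the average cluster size. It then works an example from the Guinea Ebola ring vaccination trial: "the average ring size was about 80, and the ICC was about 0.05, resulting in a design effect of about 4". From this it concludes that "600 total events would be needed for the design above, resulting in 150 effective events". The same section sets the target for mixed designs as the total of effective events.

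The preceding section, on individually randomized designs, ties 150 events per pairwise comparison to about 90% power to reject VE ≤ 30% when true VE is 60%, with a one-sided 0.025 logrank test and equal allocation.

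The Abstract assumes a 1% six-month attack rate for both kinds of population and says that "the most likely sample size is about 20,000 participants per arm".

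**The concern.** The formula, its two inputs and its result stand within a few lines of each other, and the result does not follow. The error carries straight into the 600-event figure.

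This is the only numerical inflation factor that the article gives for cluster-randomised or blended data, and effective events are what the design counts. A factor that is too small makes cluster-randomised data look more informative than they are. The effective-event target would then appear to be met too early, with less power and wider intervals than the design promises.

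**Working it through.** **Inputs.** m ≈ 80, ICC ≈ 0.05, stated design effect ≈ 4, and 600 events = 150 effective events (mixture section). Null HR 0.70, alternative HR 0.40, one-sided α = 0.025, 1:1 allocation, 150 events, power about 90% (individually randomized section).

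**Step 1: the plan's own figures.**
- 150 × 4 = 600, so the 600 follows from a factor of 4.
- The 4 does not follow from the formula: 1 + (80 − 1) × 0.05 = 1 + 3.95 = 4.95.
- It does equal m × ICC = 80 × 0.05 = 4.00, the formula without its leading 1 (and with m in place of m − 1).
- A design effect of 4 would need ICC = 3/79 = 0.038 at m = 80, or m = 1 + 3/0.05 = 61 at ICC 0.05.

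**Step 2: effective events.**
- 600/4.95 = 121.2, which is 19% below 150.
- 150 × 4.95 = 742.5, which is 24% above 600.
- Over-credit per cluster-randomised event: 4.95/4 = 1.24.
- The standard error of the log hazard ratio is larger by √(150/121.2) = 1.11, or 11%.

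**Step 3: does rounding in the inputs explain it?** Both inputs are approximate. The ranges below are assumed.

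| m | ICC | Design effect | Effective events from 600 |
|---|---|---|---|
| 80 | 0.050 | 4.95 | 121 |
| 80 | 0.045 | 4.56 | 132 |
| 75 | 0.045 | 4.33 | 139 |
| 85 | 0.055 | 5.62 | 107 |

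No combination in this range reaches 4. As a cross-check on m, the Conclusion describes the same trial's interim data as 90 rings "comprising a total of 7651 participants", or 7651/90 = 85 per ring. That points away from a smaller m.

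**Step 4: power if an all-cluster trial is analysed at 600 events.** With log ratio ln(0.70/0.40) = 0.560, power = Φ(√(D·f) × 0.560 − 1.96), where D is the number of effective events and f depends on the variance formula: 0.25 for Schoenfeld, 0.7/1.7² = 0.242 for the event split under the null, 0.4/1.4² = 0.204 for the split under the alternative. The mixed version uses the null split for the critical value and the alternative split for the spread.

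| Formula | D = 150 | D = 121 | Loss (points) |
|---|---|---|---|
| Schoenfeld | 92.9% | 86.9% | 6.0 |
| Null event split | 92.1% | 85.8% | 6.3 |
| Mixed null/alternative | 90.3% | 83.7% | 6.6 |
| Alternative event split | 87.2% | 79.5% | 7.7 |
| Exact conditional binomial | 88.4% | 78.7% | 9.7 |

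At 150 events these bracket the stated 90% or so, which supports the base calculation. The normal approximations lose about 6 to 8 points. The exact test loses more, partly because its attained level happens to be lower at 121 events (1.7%) than at 150 (2.0%). Adding the three O'Brien-Fleming looks changes little: 92.7% falls to 86.5% with the Schoenfeld variance.

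**The case against.** The best defence is that this is an illustration. The article calls the inflation one possible approach, borrows its inputs from another disease, and says in the Conclusion that cluster randomisation is less likely to be chosen and that the blended analysis needs further study. All of that is true and limits the consequence. It does not make the result follow from the formula, and no other factor is offered.

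Four stronger readings are tempting, and the document does not support them.

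- **That 600 events is the trigger for the final analysis.** The stated target is effective events; 600 is a conversion for an all-cluster trial. Power falls short only if the factor of 4 is itself used in the count.
- **That type I error is affected.** The section on blending of analysis specifies a robust sandwich variance to keep inference valid under within-cluster dependence. The error bears on how much information is collected.
- **That an all-cluster trial needs 18,062 × 4.95 ≈ 89,400 per arm at 30,000 enrolled per month.** Enrolling 2 × 89,400 = 178,800 people at that rate takes 6.0 months, longer than the 4.2 months to final analysis in that row of Table 1. Follow-up would lengthen and events would not scale in this way.
- **That the correction should use 85 per ring, giving about 780 events.** The 85 comes from that trial's interim data, and the article does not say which data its figure of about 80 describes. It is a cross-check, not a replacement input.

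On the Abstract, the body does derive 20,000 under the individually randomized heading and says that cluster designs need more. This is loose wording, not a second arithmetic error.

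**Conclusion.** The concern holds as an arithmetic error in a stated planning figure. On the article's own formula and inputs the design effect is 4.95, 600 cluster-randomised events are worth about 121 effective events, and 150 effective events need about 742.

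The power range of about 79–87% rests on three assumptions: all events come from cluster randomisation, the analysis is done at 600 events, and the design-effect approximation with m = 80 and ICC = 0.05 is adequate. In a mixed trial the shortfall shrinks with the share of cluster-randomised events. For example, 75 individually randomised events plus 300 cluster-randomised events would count as 150 with a factor of 4, but as 75 + 300/4.95 ≈ 136 with the correct one.

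**What to change.** In the section on mixtures of designs, replace the design effect of about 4 by about 5 and the 600 events by about 740–750 (150 × 4.95 = 742; 150 × 5 = 750). Use the same factor wherever cluster-randomised events are converted to effective events. If a value near 4 was intended, state the unrounded ring size and ICC that produce it.

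As a secondary wording point, say in the Abstract that about 20,000 per arm was derived for individual randomisation and does not include the design effect.

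The edit costs two figures and one clause. The real cost is that an all-cluster trial needs about 24% more events than the article now states. The analysis method and the 150-event target for individually randomised comparisons do not change.
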